### Provision

The patient as the insured will be indemnified in respect of postoperative complications stated in the schedule during the period of postoperative follow-up, physical examination, and rehabilitation guidance according to the medical accident insurance purchased preoperatively.

## Discussion

This study is designed to use patients from the Institute of Orthopedics of the Chinese PLA General Hospital to investigate a fourth-generation, tissue-engineering-oriented scaffold to construct tissue-engineered natural cartilage. Patients with full-thickness cartilage injury of the knee will be treated with the tissue-engineered cartilage, and improvement in the knee joint function, symptoms and pain, and adverse events will be observed. Microfractures will be used as controls for the comparative analysis. This trial will attempt to confirm whether tissue-engineered cartilage is more suitable for the clinical repair of full-thickness cartilage injury of the knee.

The characteristics of this study are: (1) a prospective, randomized controlled clinical trial, to observe the effectiveness and safety of autologous, cell-derived, tissue-engineered cartilage for the repair of full-thickness cartilage injury of the knee and (2) it is the first study to construct a completely natural, tissue-engineered cartilage using a tissue-engineering-oriented scaffold, for the clinical repair of articular cartilage injury of the knee, with a sample size of 100 cases. The trial results should have reliability and clinical feasibility.

This study also has some limitations: (1) because of the initial development of the tissue-engineering-oriented scaffold to build a completely natural, tissue-engineered cartilage, young patients with small cartilage defects (no larger than 5 cm^2^) will be enrolled, and further investigation is warranted to observe the therapeutic efficacy of the tissue-engineered cartilage on large-area cartilage defects in older people and (2) it is limited by a short-term follow-up (only 1.5 years), and therefore, long-term efficacy remains to be investigated. Therefore, the full clinical effect of a completely natural tissue-engineered cartilage needs to be studied further.

### Trial status

Currently recruiting.

## Appendix

**Table 2 Tab2:** Lysholm score sheet

Lysholm score			Left knee	Right knee
Claudication (5 points)	No 5	5		
	Mild or periodically 3	3		
Need support (5 points)	No 5	5		
	Cane or crutch 2	2		
	Cannot bear 0	0		
Angina (15 points)	No 15	15		
	Snagging without pain 10	10		
	Occasional angina 6	6		
	Frequent angina 2	2		
	Joint angina 0	0		
Joint instability (25 points)	No 25	25		
	Rarely 20	20		
	Frequently in heavy exercise 15	15		
	Occasional in daily life 10	10		
	Frequent in daily life 5	5		
	Each step 0	0		
Pain (25 points)	No	25		
	Rarely	20		
	Obvious during heavy exercise	15		
	Obvious after 2 km walking	10		
	Obvious within 2 km walking	5		
	Continuous	0		
Swelling (10 points)	No	10		
	Heavy exercise	6		
	Daily exercise	2		
	Continuous	0		
Stairs (10 points)	No	10		
	Mild difficulty	6		
	One step	2		
Squatting (5 points)	No	5		
	Mild difficulty	4		
	Less than 90°	2		
	Cannot	0		
		Total		

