### Outcome measures

#### Primary outcome measure

The Lysholm score for efficacy evaluation will be recorded at 12 months postoperatively. The Lysholm score [22] ranges from 0–100 points and consists of eight dimensions: a score of 80–100 points indicates elimination of all or the main symptoms, basic recovery of joint function, being capable of participating in normal labor and work (excellent); 60–79 points indicates elimination of all or the main symptoms, basic recovery or great improvement in the main function of the joint (good); and 0–59 points indicates no symptom improvement or symptom deterioration (poor). Efficiency = the number of excellent and good cases/the total number of cases × 100%.

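### As printed, the Lysholm sheet has no 0-point option for limp or stairs, so its lowest total is 5, against the 0–100 range stated for the primary outcome

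*Protocol article*

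**What the plan says.** Under Primary outcome measure, the article states: "The Lysholm score for efficacy evaluation will be recorded at 12 months postoperatively". It describes a score that "ranges from 0–100 points and consists of eight dimensions", and divides the total into excellent (80–100), good (60–79) and poor. The last band is defined by "0–59 points indicates no symptom improvement or symptom deterioration (poor". Success is then a proportion: "Efficiency = the number of excellent and good cases/the total number of cases × 100". The cut that decides success is therefore 60.

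Appendix Table 2 prints the sheet item by item, with the points for each option, a column for each knee and a total line. The limp item is headed "Claudication (5 points" and offers 5 or 3 points, the last option being "Mild or periodically 3". The item headed "Stairs (10 points" offers 10, 6 or 2. The other six items each end in a 0-point option; the locking item, for example, ends with "Joint angina 0". The article does not say how to score a patient who is worse than the last option for limp or stairs.

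**The concern.** The stated range and the printed sheet cannot both be right. An assessor who works from Table 2 has no matching answer for a patient whose limp is worse than mild or periodic, or whose difficulty with stairs is worse than the last option. The assessor must tick an option that is too favourable or leave the item blank.

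Table 2 is the only version of the primary instrument that the article shows. The total is cut at 60, and the Sample size section rests on the resulting proportions (78% and 97%). A few points are enough to turn a failure into a success for a patient close to the cut.

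**Working it through.** **Inputs.** Item options come from Appendix Table 2. The range and the cut at 60 come from Primary outcome measure.

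| Item | Highest option | Lowest printed option |
|---|---|---|
| Limp (printed as claudication) | 5 | 3 |
| Support | 5 | 0 |
| Locking (printed as angina) | 15 | 0 |
| Instability | 25 | 0 |
| Pain | 25 | 0 |
| Swelling | 10 | 0 |
| Stairs | 10 | 2 |
| Squatting | 5 | 0 |

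**Step 1, the stated range.**
- Maximum: 5 + 5 + 15 + 25 + 25 + 10 + 10 + 5 = 100. This agrees with the article.
- Minimum: 3 + 0 + 0 + 0 + 0 + 0 + 2 + 0 = 5. The article states 0.
- With a 0-point option added to limp and stairs, the minimum becomes 0 and the range matches.

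**Step 2, size of the over-score.** For a patient beyond the last option who is given that option, over-score = lowest printed option − 0:
- limp only: 3
- stairs only: 2
- both: 3 + 2 = 5

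**Step 3, who changes category.** With full-scale total T and over-score d, the patient moves from poor to good only if T < 60 ≤ T + d, that is, if T lies from 60 − d to 59:
- limp only: 57–59
- stairs only: 58–59
- both: 55–59

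A patient with the lowest possible total moves from 0 to 5 and stays in the poor category.

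**Step 4, can such totals occur?** Yes. With limp and stairs both at 0, the other six items can still reach 5 + 15 + 25 + 25 + 10 + 5 = 85. One example is support 5, locking 10, instability 15, pain 15, swelling 6 and squatting 4. The full-scale total is 55, and the printed sheet gives 55 + 3 + 2 = 60.

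**Step 5, enumeration.** Adding a 0 option to limp (3 options) and stairs (4 options) gives 3 × 4 × (3 × 5 × 6 × 6 × 4 × 4) = 12 × 8,640 = 103,680 item combinations. Of these, 51,840 include a 0 for limp or stairs and are over-scored by the printed sheet. In 2,923 the over-score carries the total from below 60 to 60 or more (2,923 / 103,680 = 2.8%). The combinations are unweighted, so this shows that crossing is possible but does not estimate how many patients would cross.

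**Step 6, scale of the outcome.** At the article's assumed rates, with 50 per arm, the expected number of poor results is 50 × 0.22 + 50 × 0.03 = 11 + 1.5 = 12.5. With 42 per arm (the stated 84 in total) it is 9.24 + 1.26 = 10.5. These are the patients among whom a reclassification could occur, not a count of reclassifications.

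**The case against.** Four objections have weight.

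*Table 2 may not be the working form.* The text shown does not refer to Table 2. Primary outcome measure defines the score by a cited instrument, and Data collection, management, and analysis places records in an eCRF that is not shown. This stands: the article does not establish that data are being collected without the two options.

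*The rows may have been lost in print or in text extraction.* This cannot be excluded. It is less likely because the other six items keep their 0 option and the maxima add to exactly 100.

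*A blank item need not do harm.* In a summed sheet an unticked item can count as 0, which would give the intended total. This also stands. Over-scoring follows only if the lowest printed option is ticked, and nothing in the article says that a blank item voids the total.

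*No bias between arms is shown.* The same sheet serves both arms, and the article describes blinded evaluators. If poor results are commoner after microfracture, as the sample size assumes, over-scoring would tend to raise control results more often and so narrow the difference. The article gives no basis for putting a number on this.

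A reader might infer that the worst patients are scored too high and that this settles the count below 60, or that with only about 10 to 13 poor results expected a few shifts will matter. The document does not support either reading. The lowest scorers remain poor, only totals of 55–59 can cross, and nothing shows that even one patient will be in that position.

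**Conclusion.** The contradiction holds on the face of the article: the printed sheet runs from 5 to 100, and the stated range is 0 to 100. None of the objections removes it, because the article prints the whole instrument and two items do not fit its own scale.

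The effect is small and conditional. It is at most 5 points per patient, and it alters the success classification only for a full-scale total of 55–59 (narrower when one item alone is affected). It rests on two assumptions: that the form in use matches Table 2, and that assessors tick the lowest printed option when no option fits. Neither can be confirmed from the document, and the number of patients affected is unknown. The point is worth settling because it concerns the scoring of the primary outcome and is cheap to check, not because a distorted result has been shown.

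**What to change.** First, compare the source form and the eCRF in use with Table 2 and confirm whether limp and stairs each carry a 0-point option.

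- If they do, correct Table 2 so that it agrees with the 0–100 range. The cost is a correction to the published table.
- If they do not, add the 0-point option to both items, after checking the sheet against the cited instrument. Then review completed forms on which the lowest printed option for limp or stairs was ticked, or the item was left blank. The review should be done without knowledge of the treatment group, and the cases changed should be documented.

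The cost in the second case is a revised form and a limited review. Trial status says that recruitment is under way, so an early check keeps the number of forms to review small. The cut at 60, the sample size and the analysis need no change on account of this point.

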## Abbreviations

dGEMRIC: Delayed Gadolinium-enhanced Magnetic Resonance Imaging of Cartilage
eCRF: Electronic Case Report Form
FCD: Fixed charge density
GAG: Cartilage glycosaminoglycan
IKDC: International Knee Documentation Committee
VAS: Visual Analog Scale
